## Abstract

**Background:**

In this paper, we present the protocol for a cluster-randomised trial to evaluate the implementation and effectiveness of a workplace mental health intervention in the state-wide police department of the south-eastern Australian state of Victoria. n. The primary aims of the intervention are to improve psychosocial working conditions and mental health literacy, and secondarily to improve mental health and organisational outcomes.

**Methods/design:**

The intervention was designed collaboratively with Victoria Police based on a mixed methods pilot study, and combines multi-session leadership coaching for the senior officers within stations (e.g., Sergeants, Senior Sergeants) with tailored mental health literacy training for lower and upper ranks. Intervention effectiveness will be evaluated using a two-arm cluster-randomised trial design, with 12 police stations randomly assigned to the intervention and 12 to the non-intervention/usual care control condition. Data will be collected from all police members in each station (estimated at >20 per station). Psychosocial working conditions (e.g., supervisory support, job control, job demands), mental health literacy (e.g., knowledge, confidence in assisting someone who may have a mental health problem), and mental health will be assessed using validated measures. Organisational outcomes will include organisational depression disclosure norms, organisational cynicism, and station-level sickness absence rates. The trial will be conducted following CONSORT guidelines. Identifying data will not be collected in order to protect participant privacy and to optimise participation, hence changes in primary and secondary outcomes will be assessed using a two-sample t-test comparing summary measures by arm, with weighting by cluster size.

**Discussion:**

This intervention is novel in its integration of stressor-reduction and mental health literacy-enhancing strategies. Effectiveness will be rigorously evaluated, and if positive results are observed, the intervention will be adapted across Victoria Police (total employees ~16,500) as well as possibly in other policing contexts, both nationally and internationally.

**Trial registration:**

Current Controlled Trials: ISRCTN82041334. Registered 24th July, 2014.

## Background

Mental health problems account for roughly a quarter of total years lost due to disability and are the third largest cause of the overall disease burden in Australia [1, 2]. The majority of these mental health problems occur in working age Australians, with one in five Australians aged 16-85 years experiencing an anxiety, affective or substance use disorder in any given year [3]. Past studies across a large number of countries have demonstrated that stressful working conditions, such as the combination of high job demands and low job control (job strain), have detrimental impacts on mental health [4–6]. In Australia, previous research has estimated a job strain-population attributable risk (PAR) for depression of 13 % among working males and 17 % among working females [7], and an associated cost burden of $730 M per year nationally [8]. This is only a fraction of the total depression-related workplace costs which have been estimated at $12.6B per annum [8]; but this fraction likely underestimates the job stressor-attributable burden of mental health problems because other job stressors (e.g., bullying, job insecurity) and other mental health problems associated with job stressors (e.g., anxiety, burnout) have not been accounted for [8]. Job stressors also predict elevated risks for poor health behaviours as well as various physical illnesses, including cardiovascular disease [9, 10].

In parallel to the growing recognition of and responses to job stress, interventions to promote mental health and mental health literacy in the workplace are gaining acceptability as a means to prevent, screen, and effectively manage depression, anxiety, and other mental health problems among employees in various industrialised countries [11–15]. Mental health literacy is defined as knowledge and beliefs about mental disorders which aid their recognition, management or prevention [16]. A prominent Australian example of this is *beyondblue’s* National Workplace Program, which aims to raise awareness of depression and anxiety as treatable illnesses, improve help-seeking behaviours, reduce stigmatising attitudes, and develop confidence and skills in providing help to people who might be experiencing a mental illness [17]. Another example is Mental Health First Aid (MHFA), which seeks to improve mental health literacy by developing knowledge and skills on how to recognise common mental disorders and provide “First Aid” support until professional help can be obtained, increase understanding about the causes of mental disorders, improve knowledge of the most effective treatments, and reduce stigma [18, 19]. There is evidence of effectiveness of MHFA from various studies [19], including randomised-controlled trials [18] and cluster randomised controlled trials [20]. In addition to improvements in mental health literacy, there is also some evidence of improvements in mental health among MHFA trainees [18]. These programs address some aspects of mental health literacy, but to date they have tended to emphasise reducing the impact of mental health conditions or providing strategies to manage mental health conditions in the long term (secondary and tertiary prevention), rather than preventing mental health conditions from occurring in the first instance (primary prevention).

In the workplace setting, primary prevention should include reduction of work-related risks to mental health, as well as enhancement of mental health-promoting aspects of work [14]. Job stress prevention features prominently here, and is relevant in all work contexts [21]. Job stress interventions have tended to focus on the primary and secondary intervention levels, whereas mental health literacy interventions have tended to focus on the secondary and tertiary levels, and the two have tended to operate independently [10]. A more integrated approach would bring these together to encompass primary, secondary, and tertiary intervention.

There is growing recognition among workplace stakeholders of the need to fulfill Occupational Health and Safety (OH&S) obligations with respect to psychological and physical health, as well as growing awareness of the impact of common mental disorders (work-related or otherwise) on productivity at work (e.g., sickness absence, presenteesim, turnover) [8, 11, 14, 22, 23]. Employers, in particular, are increasingly receptive to integrated or comprehensive approaches, as characterised above, which to some extent are practiced in Europe [24] and Canada [25], but less so in Australia and elsewhere [10, 14]. Canada’s 2013 “National standard on psychological health and safety in the workplace” represents a recent policy development aiming to promote integrated approaches to workplace mental health using a voluntary standard strategy [25, 26].

While all occupational groups are potentially exposed to job stressors, some occupations are more exposed than others. Research in the Australian context [27, 28] as well as internationally [29] has identified police work as being particularly stressful. High levels of job stressors in police have been linked to burnout, work-family conflict [30], depression, intimate partner violence [31], psychological distress [27, 28], and suicide [32]. As in other occupations, organisational sources of job stress such as high job demands (e.g., time pressures and work overload), low supervisor or collegial support [27, 28, 33, 34] and low levels of control (i.e., latitude in deciding how to do one’s work) have been found to be significant sources of stress in police [27, 28, 33]. While stress-induced mental and physical health outcomes in law enforcement may also be linked to acute operational situations and events such as attending accident scenes and exposure to violence [35, 36], evidence to date suggests that organisational sources of job stress are better predictors of police distress [37–39] than acute and potentially traumatic incidents.

There have been a number of job stress intervention studies in the police sector [40, 41]. However, these have tended to focus on improving individual responses to stressors, rather than the reduction of stressors. Given that many of the stressors experienced by police stem from both individual and organisational sources, it is appropriate to address intervention efforts at both these levels. This is further supported by the findings of systematic reviews of job stress intervention studies, which indicate that the most effective interventions combine secondary worker-directed (e.g., coping and time management skills) with primary work-directed intervention (e.g., moderation of demands, improved supervisory support) [42, 43].

The current study will be undertaken in conjunction with three partner organisations, namely Victoria Police, WorkSafe Victoria and the Victorian Health Promotion Foundation (referred to as VicHealth). Victoria Police is committed to finding more effective ways of protecting and promoting the mental health of its members and will be hosting the trial. Victoria Police is one of the largest employers in Victoria (~16,500 employees), and has one of the highest job stress-related claims burdens in the workers compensation system. The second partner, Worksafe Victoria, is the OH&S regulator and state workers’ compensation insurance provider. Worksafe is keenly interested in preventing work-related psychological harm and reducing associated claims in Victoria Police. Worksafe funds this research through the Institute for Safety Compensation and Rehabilitation Research (ISCRR). Finally, the Victorian Health Promotion Foundation, the third project partner, has a long-standing interest in workplace health promotion, and in developing new intervention strategies in the workplace setting [44]. This trial was preceded by two intervention needs assessment and development projects in Victoria Police (described below), also involving the above-named partners.

In this paper, we present the protocol for a cluster-randomised trial to evaluate the implementation and effectiveness of a workplace mental health intervention in 24 Victoria Police stations. The following main intervention effectiveness hypotheses will be tested comparing the intervention versus the control arms:There will be significantly greater improvement in the intervention compared to wait-list control arms in the primary outcomes of mental health literacy and psychosocial working conditions over a one year period;There will be significantly greater improvement in the intervention versus control arms in the secondary outcomes of mental health and organisational outcomes over a one year period;

The intervention will be targeted, and hypotheses tested, at the police station (cluster) level. The randomisation procedure, outcome measurement, and analysis will also be conducted at the station or cluster level.

## Methods/design

### Design of the study

A two-arm cluster RCT will be used to evaluate intervention effectiveness. The cluster level is defined by police stations. Twelve stations will be allocated to the intervention condition and 12 to a wait list control condition. This design was chosen because intervention activities to improve working conditions will be conducted at the workplace level, reflecting normal practice within the host organisation, thus precluding random assignment of individual participants to intervention or control within a given police station. The mental health literacy intervention is also directed at the station level, which is anticipated to affect knowledge, attitudes and helping behaviours across each participating station.

Due to resource limitations, particularly the small number of project field staff available for recruitment, data collection, and intervention implementation, the trial will be rolled out in four temporally-staggered strata of six stations each (sets of six randomly assigned to three intervention and three control stations): a staggered cluster design. A refined version of the intervention will be implemented in control stations by Victoria Police following the conclusion of the trial.

Ethics approval was granted by Human Ethics Advisory Group at the School of Population and Global Health at the University of Melbourne (ethics number: 1340429) and the Human Ethics Committee at Deakin University (Melbourne, Australia) (ethics number: 2014-132), as well as approval from Victoria Police. The study will be conducted in accordance with CONSORT guidelines [45].

### Setting and participants

Victoria Police is a large state-wide organisation comprising ~13,000 uniformed or ‘sworn’ police members and ~3500 civilian employees, operating an estimated 346 police stations across the state. Victoria has a population of 5.9 million persons and covers an area of 227,416 km^2^.

#### Recruitment of clusters

For feasibility reasons, recruitment will be restricted to the divisions of Victoria Police located in geographical regions that are within two hours’ travel time by car from the researchers’ university base; this corresponds to a large proportion of the state’s population. These divisions were selected in consultation with welfare-related departments within Victoria Police (e.g., Policy Psychology, OH&S, HR) and a steering group consisting of Assistant Commissioners, Commanders, and other senior members of Victoria Police. The inner and outer Eastern and Northwest police districts (compass direction relative to the Melbourne central business district) were chosen to obtain some variation in setting and population base (Fig. 1). The selected areas include a mix of predominantly suburban stations, with some regional sites also involved. In addition to being in the selected areas, station inclusion/eligibility criteria include a minimum size (40 or more sworn police members working in each station to achieve a participating sample of at least 20 employees) and 24-hour operation. The two stations that participated in the intervention development study preceding the trial were excluded from consideration. We recruited police stations in four strata, each consisting of six police stations (three allocated to intervention and three allocated to wait-list control). The Assistant Commissioners for the two participating districts (one per district) generated lists of stations meeting the inclusion criteria. Researchers then made contact with those stations and invited them to take part in the study.

**Fig. 1 Fig1:**
[figure not shown]
Inner and outer Eastern and Northwest police districts (compass direction relative to the Melbourne central business district) chosen to obtain variation in setting and population base

Station-level organisational data will be obtained from Victoria Police’s central HR department for nominated stations, including size (number of sworn members assigned to station), station-level unplanned absence rates, and the proportion of junior to senior members in the station (ratio of employed Full-time Equivalents of constables and senior constables to Sergeants and Senior Sergeants). These station characteristics will be considered in randomisation procedures as described below.

#### Recruitment of participants within stations

All sworn Victoria Police members within participating police stations will be invited to take part in assessments and intervention activities, including early career officers (Probationary Constables and Constables), mid-tier ranks (Senior Constables and Leading Senior Constables) and station command (Sergeants and Senior Sergeants). There are no exclusion criteria at the individual level.

Information regarding the project activities will be distributed in hard-copy leaflet and poster format in participating stations. Information sessions will also be held for station command and general staff, explaining the goals of the study, outlining what the baseline survey involves, and emphasising that participation in the survey is voluntary and anonymous. They will also be informed that their station may be randomly-assigned to receive the intervention, or that they may receive an adapted version of the intervention from Victoria Police at the conclusion of the study (wait-list control). The introduction to the questionnaire will reiterate the voluntary and anonymous nature of the survey and hence completion of the questionnaire will signify that informed consent has been gained.

### Sequence generation, randomisation and allocation concealment

Randomisation to either the intervention or control arms of the trial will be at the station level. A computer-generated randomisation list stratified by region (Inner Eastern, Outer Eastern, Inner North West, and Outer North West) will be created by a trial statistician who is not an investigator in the study. Given the small number of clusters involved, there is a risk that the randomisation process would produce an imbalance between the two treatment groups; to prevent this from occurring, the randomisation procedure will be balanced by size of police stations, mean unplanned absence rate at the station level in the six months prior to the trial, and the proportion of junior to senior members in each station [45, 46]. Study sites will be enrolled and then randomised until the required number of clusters and sample size is reached. As mentioned above, we will recruit in four strata. Within each stratum, there will be three stations allocated to intervention and three allocated to wait-list control. The sequence will be generated through a computer generated list of random numbers using Stata for Windows, version 12 (StataCorp, TX, USA) with an allocation ratio of 1:1. Participating police stations will be informed of their allocation to intervention or control conditions by researchers after completion of baseline surveys. Because random allocation will be conducted for each stratum of six stations after completion of baseline surveys, researchers and participants will be blinded to allocation up to the start of the intervention period for each stratum, after which blinding is not feasible due to the psychosocial nature of the intervention.

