### Data collection

Baseline and follow-up data will be collected at 0 and 12 months respectively using an anonymous online iPad-Mini-based survey. This method was chosen in consultation with Victoria Police, and was informed by a number of considerations. First, identifying information is not usually requested in internal surveys (which average 20–25 % response), and when they do, respondents often leave the field/s blank. It was also anticipated that members would be especially reluctant to include identifying information on a survey that includes questions about mental health. Hence we decided to forgo the collection of identifying information, greatly limiting analysis possibilities, in order to optimise response rates and representativeness in the survey data. It was not possible to use incentives due to Victoria Police anti-corruption policies.

To further address concerns about confidentiality, we will use an electronic survey method that is independent of Victoria Police IT systems. The iPads are clearly marked as Deakin University property, and anonymity and independence from the host organisation’s IT systems will be emphasised in information sessions and promotion activities, alongside information on the voluntary nature of the survey on the welcome page. One or two iPads will be left at each participating station over a period of two to three weeks, during which time the number of responses will be monitored by the researchers on the university server to which the survey data is sent. Response rate updates will be sent to the station ‘champion’ who will help promote survey participation at the stations, and will be complemented by project field staff visits timed to coincide with shift changes to promote the survey.

Individual-level survey data will be complemented by station-level data collected from station command and relevant departments (e.g., HR), and will include staffing levels, changes in key staff at participating stations, restructures, and other events or activities that could affect intervention outcomes. Finally, qualitative interview data will also be collected as detailed below.

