## Trial status

This trial has been registered with the International Standard Randomised Controlled Trial database (ISRCTN82041334), and the first of four groups of six stations was initiated in September of 2014 has been recruited, baseline surveys conducted, then randomly allocated to intervention and control conditions (3 each); follow-up data for this first stratum is currently being collected. The decision to not collect individual identifying information, along with the administration of surveys on University (clearly not linked in to Victoria Police information systems) iPads likely explains the relatively high baseline survey response rates, averaging approximately 70 % (range 53 to 88 %) across the six stations enrolled in the first stratum.

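### Baseline primary scores are in hand before each draw, but neither the allocation nor the unadjusted change-score test uses them efficiently; a baseline covariate would recover the lost precision

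*Protocol article*

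**What the plan says.** Under Sequence generation, randomisation and allocation concealment, the protocol article recognises the small-sample problem: "Given the small number of clusters involved, there is a risk that the randomisation process would produce an imbalance between the two treatment groups". Its answer is stratification by region, a 3:3 split within each stratum of six, and balancing. On the latter, "the randomisation procedure will be balanced by size of police stations, mean unplanned absence rate at the station level" over the six months before the trial, and "the proportion of junior to senior members in each station". Recruitment of clusters (text after Fig. 1) gives the source of these variables: "Station-level organisational data will be obtained from Victoria Police’s central HR department for nominated stations". None of them is a survey score.

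The same section fixes the order of events: "random allocation will be conducted for each stratum of six stations after completion of baseline surveys". Data collection adds that "the number of responses will be monitored by the researchers on the university server to which the survey data is sent". The baseline station means of the primary outcomes therefore exist before the stratum is drawn.

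The Analysis section takes the station mean before and after, forms the difference for each station, and compares the arms with a two-sample test on stations (a t-test is named), weighted by the number of individuals per station. Baseline enters only through that subtraction. The further analyses mentioned concern fidelity, reach and activities at control stations, not baseline level.

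**The concern.** With 12 stations per arm, chance differences in baseline station means are not small. A simple change score removes a baseline difference completely only if station means persist one-for-one from baseline to follow-up. If the slope is below 1, a station that starts high tends to fall back. The change score then subtracts too much, and part of the baseline difference reappears with opposite sign in the arm contrast. The plan collects the information needed to prevent this, and has it before allocation, but uses it in neither the draw nor the model. What is at stake is the precision of the primary comparison, and how a result would be read if the arms visibly differed at the start.

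**Working it through.** **The plan's own figure.** Power and sample size, Table 1, mental health knowledge: SD 3.57, difference 1.79, two-sided alpha 0.05 and power 0.90 give 84 per arm. The design effect is 1 + 19 × 0.05 = 1.95, so 84 × 1.95 = 163.8, or 164. Then 164/0.70 = 234.3 (stated 234), and 234/20 = 11.7, or 12 stations per arm. This reproduces. The document states no imbalance probability.

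**Size of the chance imbalance.** The difference of two arm means of 12 stations each has SE = √(2/12) = 0.408 station-SD. So P(|difference| ≥ 0.5) = 2(1 − Φ(0.5/0.408)) = 22.1%. Simulating constrained randomisation in four strata of six gives 21.7% when the balancing variables are unrelated to the outcome.

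**Sensitivity.** The documents do not say how far the balancing variables predict the outcomes. If they explain a share R² and are perfectly balanced, the SE is multiplied by √(1 − R²):

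| Assumed R² | P(difference ≥ 0.5 station-SD) |
|---|---|
| 0 | 22.1% |
| 0.1 | 19.7% |
| 0.2 | 17.1% |
| 0.3 | 14.3% |
| 0.5 | 8.3% |

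Balance in practice is imperfect. A correlation of 0.3 with each of three independent variables (R² = 3 × 0.09 = 0.27) gives about 18% by simulation, drawing from the best 6 of 20 allocations within a stratum. If region also explains 10% of the variance, the 22% becomes about 20%.

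**Translation to the individual scale.** At ICC 0.05 and 20 respondents the station-mean SD is √(0.05 + 0.95/20) = 0.312 individual SD. Half is 0.156, which is 31% of the planned effect for mental health knowledge (1.79/3.57 = 0.50). For supervisor support (ICC 0.019), half a station-SD is 0.130, against a planned effect of 1.4/1.38 = 1.01, or 13%.

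**Over-correction by the change score.** With pre/post station correlation r and equal SDs, a baseline difference of 0.5 shifts the expected difference in change by (r − 1) × 0.5: −0.35, −0.25 and −0.15 station-SD at r = 0.3, 0.5 and 0.7.

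**Variance of the arm difference, planned allocation.** The formulas, in station-SD² and taking the balancing variables as unrelated to the outcome, are:

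- Change score: (1 − r)² × 2/12 + (1 − r²) × 2/12.
- Baseline-adjusted: (1 − r²) × 2/12 × (1 + 1/20), where the last factor is the average cost of estimating the slope with 24 stations.

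| r (assumed) | Change score | Adjusted, formula | Adjusted, simulation | Reduction |
|---|---|---|---|---|
| 0.3 | 0.233 | 0.159 | 0.162 | roughly 30% |
| 0.5 | 0.167 | 0.131 | 0.131 | roughly 21% |
| 0.7 | 0.100 | 0.089 | 0.089 | roughly 10% |

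**What allocation alone would do.** Keep stratum 1 as drawn, and balance strata 2–4 cumulatively with one baseline score added. The SD of that score's baseline difference falls from 0.41 to 0.17 station-SD, and the exceedance from 22% to 0.1%. Mean imbalance on the three existing variables falls from 0.19 to 0.13 SD. The unadjusted change-score variance becomes 0.165, 0.132 and 0.088, almost the same as adjustment gives with the allocation left alone. With the covariate in the model, re-balancing adds only about 3–6%. An uncorrelated second primary outcome still exceeds 0.5 station-SD in about 22% of trials.

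**The case against.** The strongest reply is that nothing here is an error. The plan sees the risk, stratifies, balances on three station variables and draws after baseline. Which variables to balance is a choice, and the detail of the algorithm, including whether imbalance carries over between strata, is what an article leaves to fuller documents. That stands, and the absence of a cumulative rule is not held against the plan. The criticism is of the main test that the article does state.

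Three stronger readings are tempting, and the documents do not support them.

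- A reader might infer that baseline imbalance biases the trial. It does not. Randomisation keeps the change-score comparison unbiased on average, and the between-station error of the t-test already contains the regression to the mean. The loss is in precision and in the credibility of the one trial that is run.
- A reader might take one trial in five as a firm rate. It is close to an upper limit. Intervention development reports better mental health literacy in senior than in junior members, and links junior rank to stress over support and to workload. The junior-to-senior ratio may therefore be prognostic.
- A reader might infer that a better draw is the remedy. It would fix only the score chosen, while the article lists about a dozen primary measures, and baseline adjustment alone delivers nearly all of the variance reduction.

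It is also fair to say that prior absence, which is balanced, is close to the baseline of a secondary outcome (station sickness absence). The gap concerns the primary survey scores.

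**Conclusion.** The point holds as a matter of efficiency, not validity. Baseline primary scores are available before each draw and are used only by subtraction. The arms would start at least half a station-SD apart on a given primary outcome in up to about 22% of trials, and in about 8% if the balancing variables explain half the variance. The stated change-score test gives up roughly 30%, 21% or 10% of variance at pre/post station correlations of 0.3, 0.5 or 0.7. These figures assume 24 stations, equal SDs at both times and approximately normal station means. The correlations and the R² values are assumptions, because the documents give neither. Adjusting for baseline is well worth doing; changing the draw is optional.

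**What to change.** **Main change (Analysis).** For each outcome, replace the unadjusted change-score t-test with a station-level regression of the follow-up station mean (or the change) on arm and that outcome's baseline station mean. Keep the station as the unit and keep the planned weighting. Follow-up or change as the response gives the same arm effect once baseline is in the model. The cost is one degree of freedom (22 to 21) and a wording change made before the arms are compared. No new data are needed.

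**Optional supplement (Sequence generation), only for strata not yet drawn.** The independent statistician lists the 20 possible 3:3 allocations and scores each on cumulative imbalance, counting strata already allocated. The score covers the three existing variables plus one baseline primary score or composite named in advance. The statistician then draws at random from the best-balanced allocations. This costs a short script and requires baseline station means to reach the statistician before each draw. It adds about 3–6% precision beyond the covariate, and does nothing for uncorrelated outcomes. Trial status confirms that stratum 1 is allocated ("follow-up data for this first stratum is currently being collected") but does not say whether strata 2–4 have been drawn, so this part may no longer apply. The main change applies either way.
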